### Data Collection and Follow-Up

A transvaginal ultrasound will be performed after two weeks if the serum *β*-hCG levels are positive to confirm fetal viability and identify intrauterine pregnancies. Participants will also be referred for antenatal care after twelve weeks. Additionally, the written consent and delivery data will be confirmed from patients at the time of the study. Moreover, participants will receive information about their pregnancy outcomes through a telephone call and or *via* a text message. After the retrieval of information by participants, pregnancy outcomes including the number of babies delivered, miscarriages, and birth weights will be recorded.

### Measurement of Outcomes

#### Primary Outcome

The primary outcome will be ongoing pregnancy, *i.e.* more than 12 gestational weeks of an intrauterine living fetus verified by pelvic ultrasonography.

#### Secondary Outcomes

Positive pregnancy, *i.e.* serum *β*-hCG level ≥10 mIU/ml.Embryo implantation rate: the number of intrauterine gestational sacs observed divided by the number of embryos transferred.Clinical pregnancy, defined as an intrauterine gestational sac with fetal heartbeat detected by transvaginal ultrasonography after 6 weeks of gestation.Ectopic pregnancy, defined as a pregnancy in which implantation takes place outside the uterine cavity.Miscarriage, defined as clinically recognized spontaneous loss of pregnancy before the completion of twenty gestational weeks.Live birth, defined as the birth of at least one child with breath and heartbeat, irrespective of the duration of gestation.Low birth weight, defined as <2,500 g of a newborn’s weight.

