Furthermore, the participants’ stress and anxiety levels will be measured using a standard questionnaire before randomization and at the time of commencing FETs. In addition, the Chinese State-Trait Anxiety Inventory will be used to measure the patient’s anxiety levels (26).

On the other hand, Hormone Replacement Treatment (HRT) will be used for endometrial preparation. In addition, treatment with Estradiol valerate will commence on the third day of the menstrual cycle at a dose of 4–6 mg/day for 10–12 days. Moreover, vaginal progesterone (8% Crinone, Merck-Serono, Switzerland) will be administered at a dose of 90 mg per day, after the endometrial layer reaches a thickness of 8 mm as revealed by pelvic ultrasound scanning. FET for day three embryos will also be scheduled on the fourth day after commencing treatment with vaginal progesterone. Furthermore, at least one embryo with the best morphology, will be transferred using a soft embryo-transfer catheter with the guidance of ultrasound. Finally, the serum *β*-hCG levels will be checked fourteen days after FET.

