#### Data Analysis

The intention-to-treat analysis will be used to examine differences in the ongoing pregnancy rate and other secondary outcomes in the two treatment arms during primary analysis. In addition, multiple imputations will be used to process missing values in the data. The demographic characteristics of the two groups will also be compared. Notably, categorical variables will be compared using χ2 analysis while the Student’s t-test will be used to compare quantitative variables. Moreover, multivariable logistic regression will be used to adjust for potentially confounding factors and results, if the randomization fails to achieve two balanced groups. Such factors will include the COH protocol, number of good-quality embryos, female age at oocyte-retrieval day, number of transferred embryos, retrieved oocytes, and quality of the transferred embryos. All statistical analyses will be performed using the SPSS version 26.0 software and a p-value <0.05 will be considered to be statistically significant.

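### Chi-square on pooled embryos would ignore within-woman correlation and make p-values for the implantation rate somewhat too small

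*Protocol article*

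**What the plan says.** All references are to the protocol article.

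- **Randomization:** the unit allocated is the woman.
- **Secondary Outcomes:** the implantation rate has embryos as its denominator: "Embryo implantation rate: the number of intrauterine gestational sacs observed divided by the number of embryos transferred". Low birth weight is given as a threshold on a child's weight, with no denominator written out: "Low birth weight, defined as <2,500 g of a newborn’s weight". Live birth, in the same list, is worded per woman: "Live birth, defined as the birth of at least one child with breath and heartbeat, irrespective of the duration of gestation".
- **Interventions:** the number of embryos is bounded below only: "at least one embryo with the best morphology, will be transferred". No maximum or distribution is given.
- **Data Analysis:** the paragraph opens by covering the ongoing pregnancy rate and the secondary outcomes in the two arms, by intention to treat. It then states that "categorical variables will be compared using χ2 analysis", with Student's t-test for quantitative variables and p below 0.05 as the threshold. Multivariable logistic regression is held back for the case where randomization leaves the arms unbalanced. Its covariates include "number of transferred embryos, retrieved oocytes, and quality of the transferred embryos", so the number transferred is expected to vary. No clustered method is mentioned.
- **Data Collection and Follow-Up:** the number of babies delivered and their birth weights are recorded, so multiple births are foreseen.

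**The concern.** Two embryos placed in one uterus share the endometrium, the hormone preparation, the woman's age and the gamete source. Their outcomes are likely to be positively correlated. A chi-square test on embryos pooled by arm takes the embryo as the independent unit although the woman was randomized. It therefore credits the trial with more information than it holds.

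The stake is a falsely significant difference in implantation. The Introduction gives possible residual effects of stimulation on endometrial receptivity as the reason for postponing transfer, and implantation is the listed outcome closest to that mechanism. A spurious result could be read as mechanistic support for one timing over the other.

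**Working it through.** The plan gives no figure for the implantation rate or low birth weight, so there is nothing of its own to reproduce here. Its one calculation, 329 women per group raised to 366 for loss, concerns the primary outcome, which counts women and does not enter this check.

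**Inputs from the article:** women randomized; embryos as denominator; one or more embryos per woman; chi-square; threshold 0.05.

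**Assumed inputs (not in the documents):**
- the share *s* of women who receive two embryos, the rest receiving one: 0, 0.5 or 1;
- the within-woman correlation ρ: 0.1 to 0.3.

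**Formulas**
- Design effect: DE = [(1 − s) + 2s(1 + ρ)] / [(1 − s) + 2s] = 1 + 2sρ/(1 + s).
- True standard error / naive standard error = √DE.
- True type I error of the nominal 5% test = 2 × [1 − Φ(1.96/√DE)].

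The number of women cancels out of these ratios, so a larger trial would not remove the effect.

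| Share with two embryos | ρ | DE | True SE above naive SE | True type I error |
|---|---|---|---|---|
| all | 0.1 | 1.100 | 4.9% | 6.2% |
| all | 0.3 | 1.300 | 14.0% | 8.6% |
| half | 0.1 | 1.067 | 3.3% | 5.8% |
| half | 0.3 | 1.200 | 9.5% | 7.4% |
| none | any | 1.000 | 0% | 5.0% |

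Example for half the women and ρ = 0.3: DE = 1 + (2 × 0.5 × 0.3)/1.5 = 1.200; √1.200 = 1.095; 1.96/1.095 = 1.79; two-sided tail = 7.4%.

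**Simulation check.** A beta-binomial simulation of the chi-square test used 366 women per arm, two embryos each and an assumed implantation rate of 25% in both arms. It gave 6.2% at ρ = 0.1 and 8.2% at ρ = 0.3, close to the formula.

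**Low birth weight, if counted per newborn.** The same formula applies, with *s* as the share of deliveries that are twins. Assume twins in 10% to 30% of deliveries and a within-pair correlation of 0.3 to 0.7.
- Lowest case: DE = 1 + (2 × 0.1 × 0.3)/1.1 = 1.055, type I error 5.6%.
- Highest case: DE = 1 + (2 × 0.3 × 0.7)/1.3 = 1.323, type I error 8.8%.

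**The case against.** The strongest reply is that the article never says chi-square will be run on pooled embryos. The chi-square sentence follows one on demographic characteristics and may be a generic rule for baseline tables. The ratio could also be computed within each woman, becoming a quantitative variable with one value per woman. The t-test would then apply and the clustering problem would not arise. Variance estimation for secondary outcomes is, besides, something an unseen analysis plan often settles.

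Part of this stands: the application to pooled embryos is inferred. But the paragraph opens by covering the secondary outcomes, chi-square is the only unadjusted categorical test in it, and total sacs over total embryos is the more natural reading of the definition. The point concerns what a stated method does when followed, so it is more than a missing detail. The reserve logistic regression does not answer it. That model is conditional on imbalance, and a covariate for the number of embryos adjusts the mean but leaves the independence assumption in place.

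Several stronger readings are tempting and not supported:
- **That low birth weight is certainly affected.** Only a weight threshold is given; the per-newborn denominator and the presence of twins are inferences.
- **That reported confidence intervals will be too narrow.** The article specifies tests and a p-value threshold, and no interval for any outcome.
- **That the error rate nearly doubles.** A figure such as 9.8% needs a correlation of 0.4 and two embryos in every woman; the article fixes neither.

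**Conclusion.** The point holds in a limited form. As written, the plan leads to a test on the implantation rate that treats embryos from the same woman as independent. Under the assumed correlations of 0.1 to 0.3, the true type I error lies between 5.8% and 8.6% when half or all of the women receive two embryos.

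This rests on two conditions that the documents do not quantify: that some women receive more than one embryo, and that outcomes within a woman are positively correlated. With single-embryo transfer throughout, or zero correlation, nothing is lost. With negative correlation the test would err the other way. The first condition is permitted and foreseen by the article; the second is the natural expectation. For low birth weight the conclusion is conditional on per-newborn counting and on twins occurring.

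A reader might infer that the trial's main conclusion is in doubt. It is not, on this ground. Ongoing pregnancy is naturally one value per woman and live birth is expressly so; the sample size was computed for the former. The correction is worth making, but it concerns secondary outcomes only.

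**What to change.** In Data Analysis, state that the implantation rate will be compared with the woman as the cluster, by GEE or logistic regression with cluster-robust standard errors. State the denominator for low birth weight and, if it is newborns, treat it the same way. Keep chi-square for outcomes with one value per woman.

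Redefining low birth weight as at least one affected child per woman is not an equivalent repair. A woman with twins has two chances to meet it, so the quantity being estimated changes. If that version is wanted, it should be chosen for its own sake.

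The cost is a change of wording and a routine procedure. It needs no additional participants; embryo counts and birth weights need only stay linked to the woman. Standard errors and p-values for these outcomes become slightly larger: for the implantation rate, the standard error rises by about 3% to 14% in the cases above where half or all of the women receive two embryos.

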## Introduction

Since the early success achieved with FET three decades ago, embryo deferrals and cryopreservation have become an increasingly essential aspect of IVF treatment (1). In addition, women whose attempt at pregnancy failed after a fresh embryo transfer (ET) during a stimulated IVF cycle, often opt to immediately proceed with FET in order to get pregnant as soon as possible. However, the difference between fresh or frozen embryo transfers with regard to perinatal outcomes has been a subject of controversy. Notably, FET cycles have previously been associated with lower rates of *antepartum* hemorrhage (2), pre-term birth, ectopic pregnancy (3–6) and low birth weight (7–10). Nonetheless, FETs have been linked to higher rates of placental/hypertensive complications (5), large-for-gestational-age infants (5, 11) and inconclusive perinatal mortality rates (2, 11). Therefore, given the setbacks, most researchers are currently skeptical on the overall benefits of FET (12–15). In addition, physicians are generally questioned on ovarian hyperstimulation and the long-term effects on subsequent treatment (16). As such, FETs are often postponed in an attempt to minimize the possible residual effects of ovarian hyperstimulation on endometrial receptivity (17). However, existing literature on the area is largely scarce (18, 19) although deferrals by physicians even with the best of intentions, might frustrate couples.

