### Statistical Analysis and Sample Size Calculations

#### Estimation of Sample Size

The PASS software version 11.0 (NCSS, LLC. Kaysville, Utah, USA.) will be used to calculate the sample sizes for both groups. Notably, the ongoing pregnancy rate per FET was about 30% based on data from our reproductive center, at the time of the trial design. The calculation revealed that 329 women were to be included in each trial group to provide an 80% power to detect a minimally important absolute difference of 10% points between the immediate and delayed groups for the primary outcome of ongoing pregnancy (40 *vs* 30%) at a two­sided *α* level of 0.05. However, the trial plans to include 732 women, with 366 participants in each arm in order to account for an expected 10% loss to follow-up.

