## Discussion

In daily clinical practice, deciding on when to perform FET after a failed oocyte retrieval-ET procedure is often a dilemma. In addition, most of the patients prefer to continue treatment by postponing the transfer of their remaining cryopreserved embryos.

In a small retrospective cohort study (n = 129), Volodarsky-Perel et al. found that postponing FET by at least one menstrual cycle after a failed fresh ET was beneficial for pregnancy outcomes compared to immediate FET. This was observed if a preceding long GnRH-agonist protocol for COS was used and if an artificial preparation was indicated for FET (22). However, these results were contrary to those recently reported by a large retrospective study (n = 1,183) which revealed a similar clinical pregnancy rate in first FET cycles that were performed immediately (≤22 days) or later on (>22 days) after oocyte retrieval from the preceding failed fresh ET (21). The study concluded that deferring FET may unnecessarily prolong the time to pregnancy. Nevertheless, the results were drawn from cycles that followed failed Fresh ET using the ovarian stimulation-GnRH-ant protocol. All in all, the contradictory results from the two studies may have been due to the different protocols used for ovarian stimulation, *i.e.* GnRH analog in the failed fresh ET and in the subsequent first FET cycle.

The purpose of this randomized controlled trial is not necessarily to confirm the superiority or inferiority of immediate FET after the failure of fresh ET. On the contrary, it aims to assure both clinicians and patients that although fresh ET fails, immediate FET has no adverse effects on the eventual pregnancy outcomes, compared to delayed FET. As such, it may be beneficial in alleviating psychological pressure on patients and shorten the Time to Pregnancy (TTP) and is therefore worth trying.

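### Birth weight is recorded but listed as an outcome only through the 2,500 g cut; a comparison in grams beside it would be a cheap improvement

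*Protocol article*

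**What the plan says.** Under Data Collection and Follow-Up, the protocol article says that "pregnancy outcomes including the number of babies delivered, miscarriages, and birth weights will be recorded". The weight itself is therefore collected.

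Under Secondary Outcomes, the only entry on newborn weight is "Low birth weight, defined as <2,500 g of a newborn’s weight". Weight in grams is not listed. Live birth is listed too, but it records whether a birth occurred, not the newborn's weight.

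Under Data Analysis, the intention-to-treat analysis is to "examine differences in the ongoing pregnancy rate and other secondary outcomes in the two treatment arms", and "categorical variables will be compared using χ2 analysis while the Student’s t-test will be used to compare quantitative variables". As defined, low birth weight is categorical and goes to chi-square. The method for the full measurement is already in the plan, but no listed birth-weight outcome uses it.

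The Discussion describes the trial's purpose as assurance that "immediate FET has no adverse effects on the eventual pregnancy outcomes, compared to delayed FET".

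**The concern.** A cut in the lower tail of a measured variable uses little of what was measured. Most newborns contribute only that they were not low, and a general fall in weight shows up only through the few babies near the threshold.

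The number of births is limited as well. At the planning rate of about 30%, each arm yields roughly 100 ongoing pregnancies, so low-birth-weight events per arm would be about 5 at a 5% rate and 20 at a 20% rate. In a trial meant to reassure, an insensitive comparison errs towards reassurance: a non-significant chi-square could be the likely result even after a material general shift. At stake is how much the trial can say about newborn weight from data that it already collects.

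**Working it through.** The documents state no rate, SD, effect or power for birth weight, so there is no figure of the plan's own to reproduce. Everything below other than the number of births and the 0.05 level is an assumption.

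**Number of newborns.** Estimation of Sample Size gives the rate ("the ongoing pregnancy rate per FET was about 30% based on data from our reproductive center") and the enrolment ("the trial plans to include 732 women, with 366 participants in each arm"), with 329 per arm before the allowance for loss to follow-up.
- 0.30 × 329 = 99 and 0.30 × 366 = 110 ongoing pregnancies per arm.
- Losses after 12 weeks lower the number of newborns and twins raise it. I use 100 per arm.

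**Case A: a uniform shift in normally distributed weights.** With p the share below 2,500 g and z_p its normal quantile, the efficiency of the cut relative to the full scale is φ(z_p)² / [p(1 − p)].

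| p | φ(z_p) | Efficiency | Information lost |
|---|---|---|---|
| 5% | 0.103 | 0.22 | 78% |
| 10% | 0.175 | 0.34 | 66% |
| 20% | 0.280 | 0.49 | 51% |

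Outside that range, the loss is 84% at p = 3% and 42% at p = 30%.

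**Power in case A**, n = 100 per arm, two-sided 0.05, p = 10%, shift of d SD towards lower weight:
- In grams: Φ(d√(n/2) − 1.96). For d = 0.3, Φ(2.12 − 1.96) = 56%. For d = 0.4, Φ(2.83 − 1.96) = 81%.
- By the cut: the second proportion is Φ(z_p + d), tested by the pooled two-proportion test. For d = 0.3, 10% against 16.3% gives 26%. For d = 0.4, 10% against 18.9% gives 43%.
- For d = 0.4 at the other rates, the cut gives 32% (p = 5%) and 55% (p = 20%), against the same 81% in grams.
- With an SD of 500 g, d = 0.4 is 200 g. For 80% power the t-test needs 99 per arm; chi-square needs 353, 244 or 182 at p = 5%, 10% or 20%.

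**Case A with skewed weights.** In a simulated mixture of 90% N(3350, 430) and 10% N(2400, 600), with SD about 530 g, about 8% below 2,500 g and 100 per arm, a uniform 200 g shift gives about 75% power in grams and 22% by chi-square. Both tests reject 5% of the time under the null.

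**Case B: the harm enlarges the low-weight tail.** The mixture is the same, but the share of the low component rises in one arm.

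| Change in low component | Mean difference | t-test | Chi-square |
|---|---|---|---|
| 10% to 20% | 0.10 × 950 = 95 g | 22% | 25% |
| 10% to 25% | 0.15 × 950 ≈ 143 g | 39% | 43% |
| 10% to 30% | 0.20 × 950 = 190 g | 62% | 64% |
| Low component N(2000, 500), 5% to 20% | 0.15 × 1350 ≈ 203 g | 63% | 76% |

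For a mean difference of about 200 g, grams are far stronger in case A. In case B the two scales are level or the cut is stronger.

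**Precision at 100 per arm.**
- Proportion: 1.96 × √[2p(1 − p)/100] is about ±6, ±8 and ±11 percentage points at p = 5%, 10% and 20%.
- Grams, SD 500: 1.96 × 500 × √(2/100) ≈ ±139 g.

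**The case against.** **The loss depends on the mechanism.** A reader might infer that the cut discards half to three quarters of the information whatever timing does. The documents do not support that. They give no mechanism, and the Introduction raises pre-term birth and low birth weight, which would be harm in the low tail. Case B shows the advantage of grams vanishing or reversing there. This objection stands and limits the point.

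**The cut has its own meaning.** The proportion below 2,500 g is a usual clinical category and the one that the Introduction mentions; a mean difference is less directly clinical. A reader might conclude that the proportion should become merely descriptive. That does not follow, since it can be the more sensitive comparison. This also stands.

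**The article may simply be condensed.** The full protocol or SAP may already summarise weight in grams. That is possible, and nothing here rules it out. But the article does fix the outcome and its scale under Secondary Outcomes, so the remark concerns a stated choice, not a missing detail.

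**The reassurance is not tied to birth weight.** A reader might infer that the trial's assurance rests on a non-significant low-birth-weight test. No section says so: the trial is sized on ongoing pregnancy, and the Discussion speaks of pregnancy outcomes without naming birth weight. Nor would grams settle the matter, with 56% power at 0.3 SD. What remains is that an interval on each scale says more than either p-value.

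**Conclusion.** The point holds as a cheap improvement. Birth weight is measured, but the only listed comparison of it is through the 2,500 g cut. If timing moves weights roughly uniformly, that comparison loses about 51% to 78% of the information at assumed low-birth-weight rates of 20% to 5%, for example 43% power against 81% for a 0.4 SD shift with 100 newborns per arm and a 10% rate. If the effect is confined to the low tail, the cut is as good or better. Since the mechanism is unknown, the case is for having both scales, not for replacing one by the other.

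The figures rest on the assumed rates and distribution shapes, and on newborns treated as independent. The restriction to women who deliver and the handling of twins need care on either scale and do not decide between them. The plan contains no error or contradiction here. One secondary outcome is affected, and the conclusion on ongoing pregnancy is untouched.

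**What to change.** Under Secondary Outcomes, add birth weight in grams, reported as the mean difference between arms with its 95% CI, by the t-test already provided or a linear model.

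Keep low birth weight below 2,500 g as a compared secondary outcome, and report it as a risk difference with its 95% CI.

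Base any statement about newborn weight on both intervals, not on a non-significant chi-square.

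The cost is one line in the outcome list and one table row, with no new data. The small downside is one more secondary comparison and so slightly more multiplicity. The addition should be made before outcome data are analysed, so that it is not post hoc.
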